### Phase 3: test

Phase 3 of the PiCTuRE study will evaluate the newly co-designed, interactive, personalised digital consent platform, aiming to promote patient autonomy, shared decision-making, and personalised consent. Outcomes will be measured through both qualitative and quantitative methods, with a focus on user experience. Post-intervention, a survey and semi-structured interviews will be conducted to assess participant feedback and explore their lived experiences, including their views on discussing tissue donation for research with healthcare professionals. This phase will provide insights into the effectiveness of the intervention, with Patient Reported Experience Measures (PREMs) used to gather data on satisfaction and engagement [39, 40]. The qualitative data will help validate the quantitative findings and assess the overall success of the intervention [41]. Additionally, user feedback from post-intervention interviews will be analysed for statistical significance, contributing to the refinement of the intervention, and providing evidence for a potential new standard of care in cancer patient consent processes.

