### Barriers to tissue donation for research

The inherent vulnerabilities experienced by cancer patients often present substantial obstacles to tissue donation for research purposes [18] Several factors contribute to this hesitation among individuals living with tumours. Trust issues frequently arise, with concerns about how donated samples will be used and whether personal data will be adequately protected [19, 20] Clinical time pressures also play a significant role, as limited consultation time often precludes thorough discussions about tissue donation, leaving patients’ questions and concerns unaddressed [21]. Additionally, psychological, and social barriers can deter participation. These include fear of the unknown, such as uncertainties regarding the implications or risks of donation [21] stress and anxiety stemming from the emotional toll of their diagnosis, which can overwhelm patients and reduce their willingness to consent [22]; and a loss of confidence in the healthcare system, resulting from a diminished sense of agency or trust due to their illness experience [23]. Collectively, these barriers highlight the need for tailored approaches to engage and support patients in the donation process.

While existing studies have explored cancer patients’ general attitudes toward biobanking [19, 23, 24], there remains a critical gap in understanding the lived experiences of individuals diagnosed with primary brain or spinal tumours and their specific perspectives on tissue donation.

We suggest that the primary obstacle to advancing translational neuroscience research is not a lack of willing participants but rather the absence of effective engagement strategies, tailored communication, and appropriately timed consent processes.

Addressing these gaps is essential to ensuring access to high value biological samples, which are often removed during routine NHS procedures but remain underutilised due to barriers in the consent process. By fostering better engagement and trust, the potential for transformative research in precision oncology can be fully realised.

**PiCTuRE-** is an exploratory sequential mixed-methods study [25]. Its primary aim is to optimise support for complex patient cohorts in their decision-making processes regarding tissue donation for research through development of a digital consent platform.

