## Methods and analysis

### Objective

To design a digital intervention aimed at providing individuals with primary brain or spinal tumours comprehensive support to enhance their decision-making processes regarding tissue donation for research.

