### Phase 2: build

Phase 2 of the PiCTuRE study focuses on the development of the digital intervention through co-design methods. Patient-reported experience data will be collected and statistically analysed to validate and refine the digital consent tool [33] Co-design and experience-based co-design approaches have proven effective in enriching the development of patient-facing interventions [34–36]. To gather feedback, two Patient Reported Experience Measures (PREMs) will be used: (1) the Client Satisfaction Questionnaire (CSQ-8), an 8-item measure to assess satisfaction with the digital platform [17, 37], and (2) a 5-item Shared Decision-Making (SDM) tool, CollaboRATE [38], which asks participants to rate the quality of their provider’s communication regarding decision making.

These tools will help capture patient perspectives on the digital intervention. Data from Phase 1a and 1b, including qualitative findings, will be integrated to further personalise and refine the digital consent tool. Participants from Phase 1b will be invited to review the online tool and provide feedback, which will be used to improve the platform. The collected satisfaction and experience data will be analysed to validate items for subsequent use, guiding the next steps in the tool’s development and ensuring that it effectively meets patient needs.

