## Participant sampling and selection

The PiCTuRE study will be promoted across various digital platforms, including social media, charity websites, and patient support sites, using posters and e-flyers. Given the rarity of the target population, a multistage purposeful random sampling method [42] will be employed to encourage enrolment and identify individuals interested in participating in online semi-structured interviews, collaborating on the co-design of the digital platform, and providing feedback during the testing phase. Recognising the lack of inclusivity in research involving diverse populations, recruitment may also be supplemented through snowball sampling [43] via social media networks and outreach to ethnic community groups. Participants will receive the study information upon clicking the link provided in the online advertisements. An overview of the inclusion and exclusion criteria for all three phases of the study is outlined in Table 1.

**Table 1 Tab1:** Overview of inclusion and exclusion criteria for phases 1 to 3

Inclusion Criteria	Exclusion Criteria
Proficiency in speaking and understanding English	Inability to communicate effectively in English
Aged 18 years or older	Under the age of 18 years old
Lived experience of having a primary tumour of the brain or spine	Unable to provide informed consent
Capable of providing informed consent	No access to internet-enabled devices (e.g., smartphone, tablet, computer)
Able to communicate via digital media	Unable to communicate using digital media
Access to an internet-enabled device (e.g., smartphone, tablet, computer)	

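### Phase 3 can describe acceptability and user experience, but the plan claims effectiveness and a basis for a new consent standard, which the described design cannot support

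*Protocol article*

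**What the plan says.** **Aim.** The Objective section of the protocol article says the study is to design a digital intervention offering people with these tumours "comprehensive support to enhance their decision-making processes regarding tissue donation for research". The section on barriers to donation puts it similarly: "Its primary aim is to optimise support for complex patient cohorts in their decision-making processes regarding tissue donation for research", to be achieved by developing a digital consent platform. That section places the main obstacle in "the absence of effective engagement strategies, tailored communication, and appropriately timed consent processes", and also names limited consultation time and the stress of diagnosis.

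**Phase 3 outcomes.** The section on Phase 3 states: "Outcomes will be measured through both qualitative and quantitative methods, with a focus on user experience". On timing and method: "Post-intervention, a survey and semi-structured interviews will be conducted to assess participant feedback and explore their lived experiences". The phase is to give information on effectiveness, "with Patient Reported Experience Measures (PREMs) used to gather data on satisfaction and engagement".

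**Instruments.** They are named under Phase 2. CSQ-8 is "an 8-item measure to assess satisfaction with the digital platform". CollaboRATE is a 5-item shared decision-making tool on which participants rate how well their provider communicated about the decision. The Data analysis section carries the same type of data into Phase 3, to be compared statistically with the corresponding Phase 2 data.

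**Who is tested.** Table 1 applies one set of criteria to all three phases. The disease criterion is "Lived experience of having a primary tumour of the brain or spine". The General design section describes the population as people who are considering donation or have already donated. The Sample size section allows up to 6 test users.

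**What is claimed.** The Phase 3 section expects information on effectiveness and evidence towards a possible new standard of care for consent in cancer. The Phase 3 analysis text expects the combined data to allow a comprehensive assessment of the tool's effectiveness.

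**The concern.** A claim that a decision-support tool is effective is a claim that people decide better, or understand more, with it than without it. Phase 3 as described yields opinions of the tool and of provider communication, collected after use, from people who may or may not have a donation decision ahead of them. High satisfaction in such a group is compatible with any effect on understanding or certainty of choice, including none.

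If the plan is followed as written, the final report could present favourable ratings from at most 6 users as evidence of effectiveness and as support for changing consent practice. The study can still deliver what a development project should: a tool that users find acceptable. What is at stake is the conclusion drawn from Phase 3.

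**Working it through.** This is mainly a comparison of claims with design, so the texts are set side by side first. The arithmetic that follows is context.

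**1. What an effectiveness claim needs, and what is described**

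| Element | Described for Phase 3 |
|---|---|
| A measure of the decision, such as understanding of donation or certainty of choice | None named. CSQ-8 rates satisfaction with the platform; CollaboRATE rates the provider's communication. Survey and interviews concern feedback, lived experience and views on discussing donation with professionals |
| A reference without the tool | No measurement before use and no group without the tool is described |
| A comparison that isolates the tool | Phase 3 scores against Phase 2 scores, where Phase 2 users are also reviewing the tool |
| Testers facing the decision | Not required by Table 1; past donors are expressly part of the study population |

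**2. What the Phase 2 comparison estimates**

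Quantity of interest = result with the tool − result without the tool.

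Planned contrast = Phase 3 score on the tool − Phase 2 score on the tool.

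The second term of the first line is not observed. The planned contrast can at most show whether users rate the Phase 3 version differently from what was reviewed in Phase 2. The iterative cycles mentioned in the Abstract add no measurement before use.

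**3. Share of testers facing a decision**

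No criterion limits time since surgery or requires a pending decision, so the number of testers past the decision may be anything from 0 to 6. The document does not allow it to be narrowed.

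**4. Sample-size context**

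The only calculated sample size in the article is for the Phase 1a survey: 1.96² × 0.03 × 0.97 / 0.05² = 44.7, rounded up to the stated 45. It reproduces, but has no bearing on Phase 3, for which no precision, effect size or power is stated.

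For Phase 3, assume the maximum of 6 users.
- All 6 favourable: exact 95% interval with lower limit 0.025^(1/6) = 0.54, so 54% to 100%.
- 3 of 6 favourable: exact 95% interval 12% to 88%.

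For Phase 3 against Phase 2, assume 6 users in each phase and a two-sided 5% t test. The article does not say whether the same people take part, so both cases are shown.
- Different people (10 degrees of freedom, noncentrality d × √(6/2)): 80% power needs d = 1.80 SD. Power is 12% at 0.5 SD and 24% at 0.8 SD.
- Same people, paired (5 degrees of freedom, noncentrality d × √6): 80% power needs 1.43 SD of the differences.

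The mismatch in steps 1 and 2 would remain at any sample size.

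**The case against.** The strongest reply is that this is a development study. The objective is to design a tool, the primary aim is pursued through developing a platform, and the Abstract describes Phase 3 as refining the intervention. For that purpose user experience and interviews are ordinary outcomes, and people with past experience are a declared and sensible choice in a rare disease. This stands.

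Four stronger readings are tempting, and the document does not support them.
- *That the study's objective goes unmeasured.* The objective is to design a tool, not to demonstrate better decisions. The fault lies in the claims attached to Phase 3.
- *That no measure touches decision-making.* CollaboRATE is a shared decision-making instrument, and the comparison with Phase 2 implies that it is used again in Phase 3. It rates the provider's communication, however, so it measures neither understanding nor certainty. A tester with no current consultation about donation has nothing current to rate.
- *That nothing is recorded before use.* The article is condensed, and the Phase 3 survey items and interview guide are not shown. What can be said is that no measurement before use is described and that the survey is placed after the intervention.
- *That testers will be past their decision.* They may be. Nothing in the criteria settles it either way.

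The reply does not reach the explicit statements on effectiveness and standard of care. Interviews may show whether users felt supported, but that is a perception after the event with no reference point.

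**Conclusion.** The concern holds as a mismatch between stated conclusions and described design. Phase 3 can support statements on acceptability and user experience. It cannot support the claims of effectiveness or of evidence for a new standard of consent, because the described outcomes are post-use experience measures, the only comparator is other people's or the same people's review of the tool, and testers need not be facing the decision.

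Its size is that of a claim, not of a number: three statements in two sections go beyond what at most 6 users, measured in this way, could show. The intervals and detectable differences above rest on the assumption of 6 users per phase; the conclusion does not depend on them. It does rest on the article describing the Phase 3 measures faithfully. A full protocol with a decision-specific measure before and after use would soften it, though such a measure in people not facing the choice would still not establish effectiveness at real consent.

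The study can proceed; the wording should be corrected before Phase 3 is run and reported.

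**What to change.** 1. In the sections on Phase 3 and on the Phase 3 analysis, state the conclusion as acceptability and user experience. Remove the claims about effectiveness and a new standard of care. This costs only wording and a more modest claim.
2. Record for each tester whether they are before or after their own surgery and their own donation decision, and interpret CollaboRATE accordingly. This costs one or two questions.
3. As a low-cost addition, give a short set of items on understanding of donation and certainty about a standard hypothetical choice immediately before and immediately after use of the platform. Report each person's change descriptively, as change within the session and not as evidence of effectiveness at real consent. This costs a few minutes per tester and no extra participants. The drawback is that answering the same items twice may itself move the answers.

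Steps 1 and 2 are sufficient to resolve the mismatch. Step 3 adds information closer to the tool's purpose but does not restore the effectiveness claim, since a hypothetical choice cannot show that a real one was supported.

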## Sample size

The small sample size in this study reflects the rarity of the patient cohort, influenced by factors such as the low prevalence of the tumour type, delays in presentation and diagnosis, and post-treatment survival rates.

Recruitment and sample size will be guided by the principle of data saturation [44]. Hennink and Kaiser [45] suggest that qualitative data saturation is achieved with 9–17 participants for semi-structured interviews and 4–8 participants for focus groups.

**Phase 1a: Online Survey**– Up to 45 participants.**Phase 1b: Semi-structured Online Interviews**– Up to 10 participants.**Phase 2: Co-design Users**– Up to 6 participants.**Phase 3: Test Users**– Up to 6 participants.

To determine the sample size for Phase 1a, a calculation [46] was conducted using a 95% confidence level, a 5% margin of error, and an estimated population proportion of 3% within a population of 67 million. Based on these parameters, a sample size of 45 participants was deemed sufficient.

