### Phase 1b

Audio recordings from online interviews will be transcribed verbatim using professional transcription services to ensure accuracy and consistency. The transcriptions will then be processed in qualitative analysis software (NVivo) for detailed examination and coding. Thematic analysis [32] will be employed as the primary methodology, relying on a thorough textual analysis of the transcribed content to generate a precise and reliable dataset for subsequent analysis.

### Phase 2

PREMs outcome data will be analysed using a Statistical Package for the Social Sciences (SPSS). Correlation analysis will identify relationships between variables using correlation coefficients. Regression models will evaluate the impact of multiple variables on specific outcomes, while an Analysis of Variance (ANOVA) will assess statistically significant differences between groups. Quantitative data will be supplemented by content analysis [2, 30] of audio collected via the online co-design group sessions.

Sequential data analysis will examine the connections between findings from Phase 1 and Phase 2. These results will be triangulated to guide and inform the implementation of Phase 3.

### Phase 3

Post-intervention user experience data collected via PREMs will be analysed using the methodology outlined in phase 2 and statistically compared to the corresponding phase 2 data. Quantitative findings will be enriched by qualitative insights obtained from post-intervention online semi-structured interviews. The integration of mixed-methods data [38, 44] will facilitate a comprehensive assessment of the effectiveness of the newly developed digital tool.

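### Phase 3 interview feedback from at most 6 test users is to be tested for significance as evidence for a potential new standard of care; this is out of line with the analysis section and beyond what the design can support

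*Protocol article*

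**What the plan says.** The Phase 3: test section describes the data source: "Post-intervention, a survey and semi-structured interviews will be conducted to assess participant feedback and explore their lived experiences". It gives the qualitative data a supporting role beside the PREMs, then adds that "user feedback from post-intervention interviews will be analysed for statistical significance". In the same sentence this is said to help refine the intervention and to go towards "providing evidence for a potential new standard of care in cancer patient consent processes".

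The Sample size section sets the numbers: "Phase 3: Test Users– Up to 6 participants" and "Phase 2: Co-design Users– Up to 6 participants". It says that size follows data saturation, and it cites a saturation range of 9–17 participants for semi-structured interviews.

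The Data analysis section, under Phase 3, says that the PREM data are analysed as in Phase 2 and "statistically compared to the corresponding phase 2 data". For the interviews it says: "Quantitative findings will be enriched by qualitative insights obtained from post-intervention online semi-structured interviews". It names no significance test for them.

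**The concern.** A significance test needs a variable, a null value and a comparison. Semi-structured interview text supplies none of these by itself, and nothing in the article's Phase 3 analysis treats the interviews as anything but qualitative. The design section therefore commits the study to an inferential step on qualitative data that the analysis section does not carry.

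The result is also tied to a statement about a potential standard of care. With at most 6 users, no concurrent control and a purposefully recruited sample, a p-value from the interviews would look more authoritative than it is. A non-significant result would say almost nothing. What is at stake is how Phase 3 is reported: a formative test could be read as inferential support for changing consent practice.

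**Working it through.** **Step 1. The two sections side by side.**

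| Item | Phase 3: test | Data analysis, Phase 3 |
|---|---|---|
| PREMs | Used for satisfaction and engagement | Analysed as in Phase 2 and compared statistically with Phase 2 |
| Interviews | Support the quantitative findings; in addition, analysed for significance | Enrich the quantitative findings; no test named |

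The significance step for interviews appears only in the left column. The analysis section neither repeats it nor excludes it.

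**Step 2. Does any stated calculation cover Phase 3?** The only calculation in the article is for the Phase 1a survey. With 95% confidence, a margin of 5% and a proportion of 3%:

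n = 1.96² × 0.03 × 0.97 / 0.05² ≈ 44.7, rounded up to 45.

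This reproduces the stated 45, and correcting for a population of 67 million changes nothing. It does not extend to Phase 3. There the 6 is a cap, with no alpha, effect size or power given, and it lies below the cited 9–17 saturation range for interviews.

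**Step 3. What could a test on 6 people show?** The article defines no test variable, so this step rests on my own assumptions: each user's feedback is coded favourable or unfavourable, the null value is 50%, and the test is two-sided at 0.05. Intervals are Clopper-Pearson; p-values are exact binomial.

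| Favourable | Exact 95% CI | p against 50% |
|---|---|---|
| 6 of 6 | 54.1% to 100% | 2 × (1/64) = 0.031 |
| 5 of 6 | 35.9% to 99.6% | 2 × (6 + 1)/64 = 0.22 |
| 4 of 6 | 22.3% to 95.7% | 2 × (15 + 6 + 1)/64 = 0.69 |

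The lower limit for 6 of 6 is 0.025^(1/6) = 0.541. A favourable result is significant only if it is unanimous. The chance of 6 of 6 is 0.8⁶ = 26% if the true favourable rate is 80%, and 0.9⁶ = 53% if it is 90%.

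**Step 4. What does the design allow?** Participant sampling and selection describes a multistage purposeful random method, fed by online advertising and possibly supplemented by snowballing. Those who enter are volunteers who respond to adverts or are referred. No concurrent control is described. The only comparison is of PREMs with those of at most 6 co-design users in Phase 2. Such a design can inform usability and refinement. It cannot show that a consent process should become standard.

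**The case against.** The strongest reply is that the clause is one loose sentence in a design overview, and that the PREMs were meant. Phase 3 also collects a survey and PREMs, and the analysis section already puts the statistics there. If so, the sentence is misworded and still needs correcting. Moving the claim to the PREMs would not rescue it. Assuming two-sided alpha 0.05, 6 against 6 independent users give 24% power at a standardised difference of 0.8, and 80% power only at 1.80. If the same users supplied both phases, which the article does not say, the paired figure is 1.43 standard deviations of the difference.

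Several stronger readings are tempting and are not supported:

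- A reader might infer a flat contradiction. The analysis section is silent on testing interview data and does not forbid it. The test is stated in one place and absent from the other.
- A reader might infer that Phase 3 is meant to establish a new standard of care. The sentence says potential, and mentions refinement first. The study is called exploratory, and the small sample is acknowledged.
- A reader might infer that codes will be counted and chosen for testing after the transcripts are read. Nothing in the article describes this.
- A reader might infer that significance is impossible with 6 people. It is not, as 6 of 6 shows. The problem is imprecision and low power, on top of the data type.
- A reader might fault the article for giving no coding scheme or hypothesis. A condensed article may leave these to a fuller document. The point rests on what is stated, not on that omission.
- A reader might infer that the testers have no link to a donation decision, because Table 1 does not require one. The General design section describes the population as people considering donation or who have donated.

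What stands is that the sentence, followed as written, applies inference to qualitative data from at most 6 people and attaches a claim that the design does not support.

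**Conclusion.** The point holds in this limited form. The design section commits to a significance analysis of interview feedback that is out of line with the qualitative role given to the interviews in the analysis section. The claim attached to it goes beyond an uncontrolled, purposefully recruited group of at most 6.

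The size of the problem can only be illustrated, because the article defines no test. Under the assumed yes/no coding against 50%, even complete agreement leaves the true share anywhere from 54% to 100%, and a single dissenter removes significance. The conclusion does not depend on that illustration. It follows from the type of data, the cap of 6 and the absence of a control. The clause governs no stated primary endpoint or safety decision, but it does govern what Phase 3 may claim, so it should be corrected before Phase 3 is analysed.

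**What to change.** In Phase 3: test, delete the clause "user feedback from post-intervention interviews will be analysed for statistical significance". State instead, in line with the analysis section, that Phase 3 interviews will be analysed qualitatively, to refine the platform and to help interpret the PREMs.

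Replace "providing evidence for a potential new standard of care in cancer patient consent processes" with wording such as: providing preliminary evidence on acceptability and user experience.

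The change is a matter of wording. It needs no further participants, data or time, and the planned PREM comparison is left as it is. The downside is a more modest stated conclusion for Phase 3.
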